**For the whole trial:**

High range of complications in interventional group compared to the control group (we are going to audit the study every 3 months, discussing this point), unexpected adverse reactions to the medical products without correction possibilities, clear statistical benefit of “flush-out” treatment.

**
Frequency and plans for auditing trial conduct
**

The medical centers of clinical trial will undergo an audit twice a year by a study manager, KKS, Martin-Luther-University Halle-Wittenberg. To ensure the quality of data and study performance, the sponsor may conduct site visits by an independent auditor. An audit will be performed only after notification and arrangement with the investigator. An audit certificate will be issued as quality proof and has to be filed in the trial master file and as a copy in the investigator-site file.

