**Sample size and Statistic**

The sample-size calculation was based on the primary outcome (binary yes/no) survival without major morbidities (severe bronchopulmonary dysplasia (BPD), and/or grade 3 or 4 intraventricular hemorrhage (IVH 3–4), and/or necrotizing enterocolitis (NEC) and/or cystic periventricular leukomalacia (cPVL)).

The intervention is expected to prolong the gestation by around two weeks, resulting in an increase of the one-year survival rate without major morbidities after 27 gestational weeks of 67% (hazard = 0.0334). Based on Chen et al. (2016), the one-year survival rate without major morbidities after 25 weeks of gestation is around 36% (hazard = 0.0851) [23]. To be more conservative, the sample-size calculation was based on a hazard = 0.035 for the interventional group. Using a recruiting period of 21 months (four women per month) and an individual follow-up of one year, 34 women are needed in each group for a two-sided log-rank test with 5% significance level, a power of 80% and a loss-to-follow-up rate of 10% per year (hazard = 0.0088). Calculations were performed by PASS software.

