**Adverse event reporting harms**

The Data Safety Monitoring Board (DSMB) will follow the progress of the clinical trial; evaluate the safety and primary efficacy parameters; and will propose to the sponsor whether to continue, modify or stop a trial and provide the funding agency with information and advice. The DMSB will set up telephone conferences twice a year to evaluate current safety data. Therefore, the sponsor will provide up-to-date safety data, including a summary of AEs, line listing of SAEs and adverse device effects (ADEs). In case of a high number of severe unexpected events in between DMSB meetings or a case of a Suspected Unexpected Serious Adverse Reaction (SUSAR) or other medically important conditions, the DMSB will be informed by the sponsor immediately and may give advice for further procedures if required. An interim analysis is not planned.

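### The protocol lets the whole trial stop for statistical benefit but plans no interim analysis and sets no boundary, so the 5% error rate is not protected

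*Protocol article*

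**What the plan says.** Four statements in the protocol article bear on this.

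- *Stopping rules, For the whole trial*: one reason for stopping is "clear statistical benefit of “flush-out” treatment". No threshold, timing or boundary is attached. The same list has a complications criterion, with the remark "we are going to audit the study every 3 months, discussing this point".
- *Adverse event reporting harms*, on the DSMB's remit: it will "evaluate the safety and primary efficacy parameters; and will propose to the sponsor whether to continue, modify or stop a trial".
- *Adverse event reporting harms*, on scheduling: "The DMSB will set up telephone conferences twice a year to evaluate current safety data". The section ends with "An interim analysis is not planned".
- *Sample size and Statistic*: 34 women per group for a "two-sided log-rank test with 5% significance level" and 80% power. No allowance for interim testing is mentioned.

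**The concern.** Statistical benefit before the end of the trial can only be established by comparing the arms on outcome data, and that comparison is an interim efficacy analysis. The article therefore creates an efficacy stop, names a body that could trigger it, and says elsewhere that no such analysis is planned.

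If the stop is used, the final 5% test is no longer the only route to a positive result, and the overall false-positive rate depends on looks that nobody has defined. The trial has 68 women and one primary test. A stop on this ground would give a p-value with no defined error rate. If it came early, it would also rest on few infants followed to one year, where crossing an informal threshold tends to overstate the effect.

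**Working it through.** **1. Is the stated sample size a single-analysis design?**

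Inputs from *Sample size and Statistic*: monthly hazards h1 = 0.0851 and h2 = 0.035, dropout hazard d = 0.0088, 21 months of accrual, 12 months of follow-up, two-sided 5%, power 80%.

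- Hazard checks: −ln(0.36)/12 = 0.0851; −ln(0.90)/12 = 0.0088; exp(−0.035 × 12) = 0.657; hazard ratio 0.035/0.0851 = 0.411.
- Event probability: P(h) is the average of h/(h+d) × [1 − e^(−(h+d)t)] for t uniform on 12 to 33 months, that is, with follow-up to study end (an assumption). P(h1) = 0.778 and P(h2) = 0.490.
- Lachin-Foulkes, with φ(h) = h²/P(h) and h̄ the mean hazard: n per arm = {[1.96√(2φ(h̄)) + 0.842√(φ(h1)+φ(h2))]/(h1−h2)}² = 34.6.
- Brackets: Schoenfeld 40/(0.778+0.490) = 31.5; Freedman 46/(0.778+0.490) = 36.3.
- Simulated log-rank power at 34 per arm is 82.7%.

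The stated 34 is thus approximately reproduced by a fixed design with one final test, with nothing set aside for earlier looks.

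**2. Error rate if the benefit criterion is used**

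The article gives neither the number of looks nor the threshold, so both are assumptions here. For K equally spaced looks including the final one, Z_k is the sum of k independent standard normal increments divided by √k (400,000 simulated paths). The final test is always |Z| > 1.96.

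| Looks incl. final | Interim p<0.05, either direction | Interim p<0.05, benefit only | Interim p<0.01 | Interim p<0.001 |
|---|---|---|---|---|
| 2 | 8.2% | 6.6% | 5.4% | 5.0% |
| 3 | 10.6% | 7.8% | 5.8% | 5.0% |
| 6 | 15.4% | 10.2% | 6.7% | 5.1% |
| 11 | 20.1% | 12.5% | 7.8% | 5.2% |

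The last two columns count either direction. Check on the first row: by symmetry the benefit-only figure is the final 5% plus half the excess, 5% + (8.25% − 5%)/2 = 6.6%.

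**3. The same question in a trial-like setting**

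Equal spacing of information is not realistic here. A log-rank simulation used 68 women, hazard 0.0851 in both arms, dropout 0.0088, 12-month follow-up, and unadjusted p<0.05. Looks with fewer than 10 events were skipped, and 8,000 trials were run per setting.

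| Setting | Either direction | Benefit-only interim stop | Final test alone |
|---|---|---|---|
| 6-monthly, 33 months | 12.4% | 8.7% | 5.1% |
| 3-monthly, 33 months | 14.9% | 9.9% | 5.0% |
| 6-monthly, 46 months | 13.1% | 9.1% | 5.1% |
| 3-monthly, 46 months | 16.3% | 10.7% | 4.9% |

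The 33 months are 21 + 12. The 46 months are the 34 months from March 2021 to January 2024 (*Trial Status*) plus 12.

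**4. How much one-year outcome would an early stop have?**

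*Outcomes* places the primary outcome one year after delivery. Assume even accrual and, as an upper bound, delivery at once after randomization.

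- 21-month recruitment: when recruitment ends, only women enrolled by month 9 can have the outcome, 9/21 = 43%.
- 34-month recruitment: half of the 68 are enrolled by month 17, so half the outcomes are complete at month 29 at the earliest. At month 34 the share is at most 22/34 = 65%, or about 20/34 = 59% if delivery comes up to 7 weeks after randomization.
- In either case no one-year outcome is complete during the first 12 months.

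**The case against.** **The schedules belong to safety.** A reader might infer that efficacy is tested every three or six months, and so quote an error rate of 17% to 20%. The text does not say this. The three-monthly audit is attached to the complications criterion, and the twice-yearly DSMB calls are described for safety data. The only link between recurring review and efficacy is the DSMB's general remit over primary efficacy and its power to propose stopping. This objection stands. So does its companion: with an outcome known a year after delivery, eleven equally informative looks within recruitment could not occur.

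**The threshold is not p<0.05.** The criterion asks for *clear* benefit. If that meant p<0.001, the inflation would be negligible. This also stands, and it is why no single figure can be given. A false-positive rate several times the nominal one is possible but not shown.

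**The no-interim statement may govern.** If it does, there is one final test and 5% holds. Hence the right wording is that 5% is not protected, rather than that it fails. But then the benefit criterion has no function and should go.

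**The details may sit in an analysis plan or DSMB charter.** This does not answer the point. A boundary set out elsewhere would itself contradict the statement that no interim analysis is planned. The defect is a conflict between two statements in this article, not a missing detail.

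**An early stop need not rest on a minority.** This is correct. Late in a 34-month recruitment, more than half of the outcomes could be complete, so the point needs a condition on timing.

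**Conclusion.** The contradiction is certain: *For the whole trial* allows an efficacy stop, *Adverse event reporting harms* rules out an interim analysis, and *Sample size and Statistic* spends the full two-sided 5% on a fixed design. If the benefit criterion is used as written, the error rate is uncontrolled.

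The size is conditional on what the article leaves open. With unadjusted p<0.05, one interim look gives 6.6% to 8.2%, and 6-monthly to 3-monthly looks over 33 months give about 9% to 15%. With p<0.01 at 5 to 10 interim looks the error is about 7% to 8%, and with p<0.001 about 5.1% to 5.2%. The documents support neither a fixed schedule of efficacy looks nor any one of these figures.

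The limited follow-up behind an early stop is a second and weaker reason. It applies throughout a 21-month recruitment, and before about month 29 of a 34-month one. The contradiction must be resolved before any outcome comparison is made.

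**What to change.** Preferred: delete the benefit criterion from the whole-trial stopping reasons, which brings that list into line with "An interim analysis is not planned". This costs one phrase, and a single final test then has its nominal error (simulated 4.9% to 5.1%). The DSMB need not be barred from outcome data. It can still weigh benefit against risk, which matters because the primary outcome combines survival and serious morbidity; it would simply have no efficacy stop to invoke.

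Alternative, if the sponsor wants an efficacy stop: pre-specify one look, on infants with a completed one-year outcome, under a Haybittle-Peto or O'Brien-Fleming boundary, and correct the no-interim statement. With one interim look at p<0.001 and a final test at 5%, the simulated overall error is 5.0%; an alpha-spending boundary holds 5% exactly. The cost is one or two sentences and a negligible loss of final alpha.

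Such a look may save little. Under 21-month even accrual, half of the one-year outcomes are complete no earlier than month 10.5 + 12 = 22.5, after recruitment has closed. Under the 34-month window it is month 29.

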**Ethics approval and consent to participate**

The study will be conducted in compliance with the Declaration of Helsinki and all amendments.

The TRIAL obtained permission from the Ethical Committee of the Halle University Medical Center (2020-185, 25 January 2021).

Written informed consent of the patients, as well as the parents, is required for enrolment in the study and can be withdrawn at any time, without reasons or disadvantages. Eligible women with classic mid-trimester PPROM will be asked for their written informed consent at the time of admission to the hospital, after having received oral and written information. Patients, who are not able to understand the informed consent will not be included. Recruitment for the “flush out” method via a port-system is ethically sound for PPROM patients with oligo/anhydramnion based on the available research evidence.

In case of complications, all equipment for emergency interventions will be easily accessible in the perinatal centers. Only hospitals which possess a Level 1 perinatal center in accordance with German law (tertian perinatal center) will receive permission to participate in this trial.

Any modifications to the protocol will be sent to the ethics committees before they are implemented within the study, and communication changes that impact the patients would require signing of a revised consent form.

**Trial Status:**

Protocol number KKSH163, Version No. 1.0, 27 October 2020.

Recruitment began: March 2021.

The approximate date when recruitment will be completed: January 2024.

## 6. Discussion and Review of the Literature

Mid-trimester preterm premature rupture of membranes (PPROM), together with oligohydramnios before 26 weeks, affects about 0.4–0.7% of all pregnancies. A high number of unreported cases should be expected in cases of PPROM prior to 22 weeks of gestation. Mid-trimester PPROM with anhydramnion is associated with a very high neonatal mortality rate, as well as an increased risk of long- and short-term severe neonatal morbidities; physical and developmental disabilities, including chronic respiratory disease, neurodevelopmental or behavioral effects (impairment of visual/hearing/executive functioning, global developmental delay and psychiatric/behavioral sequelae); and cardiovascular diseases [3,4,24]. The early birth due to PPROM with anhydramnion during the canalicular stage of the lung development between the 16th and 26th week of gestation leads to pulmonary hypoplasia [4,25]. Prolonged anhydramnion after PPROM is associated with a four-fold increased risk of composite adverse outcomes, including death, BPD, severe neurological disorders and severe retinopathy, when compared to an age-adjusted control group [8,26].

The causes of the mid-trimester PPROM are multifactorial, including local infiltration by bacteria with reaction of pro-inflammatory cytokines, pathologic anatomical remodeling of the amniotic membranes (contribution of MMPs), invasive procedures and fetoscopic surgery, genetic and iatrogenic factors, smoking, vaginal bleeding, etc. [4,7,27,28,29,30,31,32,33]. Inflammatory mediators likely play a causative role in both the disruption of fetal membrane integrity and activation of uterine contraction.

The diagnosis of PPROM is classically established by the identification watery leakage from the cervical canal, positive swab assay for placental alpha macroglobulin-1 and indigo carmine tests [4,34,35]. The management of the PPROM requires balancing the potential neonatal benefits from prolongation of the pregnancy and reduction of the adverse effects of newborn immaturity with the risk of intra-amniotic infection and its consequences for the mother and infant [2,4,22,36]. Close monitoring for signs of chorioamnionitis (e.g., body temperature, CTG, CRP, leucocytes, IL-6, procalcitonin and amniotic fluid examinations) is necessary to minimize the risk of neonatal and maternal complications.

Despite the fact that broad-spectrum antibiotics are routinely used in the therapy of PPROM based on the guidelines’ recommendations, it must be considered that the maternally applied drugs only hardly reach the place of bacterial colonization [4,19,22]. The amniotic membranes and the umbilical cord do not have an effective capillary net which would supply the surfaces with the antibiotics from the maternal circulation [37]. The placenta is a selective barrier for foreign substances, and the bioavailability among antibiotics is very low for most antibiotic agents [4,38,39,40,41,42,43]. On the other hand, the healthy fetus without any infection after PPROM probably does not need any longtime trans-placental antibiotic treatment that can lead to a possible change of fetal programming [4,12,13,44].

The Cochrane Library and the databases MEDLINE, PubMed, EMBASE, the Cochrane Library, DRKS and ICTRP were searched. To assess the methodological quality of the study, the articles are classified on the basis of the level of evidence (LoE).

Inclusion search criteria:

PPROM and amnioinfusion and treatment (non-diagnostic)

Exclusion criteria:

The exclusion criteria included surgery, diagnostic amnioinfusion, polyhydramnion, prophylactic amnioinfusion, term pregnancy, amnioinfusion during labor, relieving variable decelerations, transcervival amnioinfusion, dilute thick meconium-staining of the amniotic fluid, external cephalic version, amnioinfusion in connection with Amniocentesis, ex utero intrapartum therapy (EXIT) procedure and reviews older than 10 years; moreover, a publication was excluded if a more recent study from the same center or author was included. Only articles published in English or German were considered (Table 2).

A search of the literature in different search contexts revealed 82 hits, resulting in 28 relevant publications, consisting of reviews, randomized clinical trials (RCTs), non-randomized/observational clinical trials and case studies, outlining the state-of-the-art of serial or continuous transabdominal amnioinfusion in most cases by using standard infusion solutions that are used off-label in this regard. The positive effects of serial amnioinfusion were neonatal death RR 0.33 (0.14–0.66, moderate quality of evidence), neonatal sepsis/infection RR 0.26 (0.11–0.61, moderate QI), pulmonary hypoplasia RR 0.22 (0.06–0.88, low QI) and maternal puerperal sepsis RR 0.20 (0.05–0.84, QI moderate) [45].

Tranquilli et al. reported that serial transabdominal amnioinfusions (AIs) could prolong the latency period to a median of 21 days [46]. De Santis et al. found out that the patients with PPROM did not appear to demonstrate any benefit from this repetitive amniotic-fluid (AF) replacement (250 mL per intervention), as measured by post-procedure AFI, because fluid loss occurred within 6 h of instillation [19].

Locatelli et al. found that the serial AI could improve the neonatal outcome primarily by prolonging latency [16,47]. The patients with PPROM and oligohydramnios had a significantly shorter interval to delivery, lower neonatal survival of 20%, 62% of pulmonary hypoplasia and 60% rate of neurological handicap [16,47].

During a Canadian study [24], for infants delivered at 23 weeks of gestation, perinatal mortality was 89.9%, and of live-born neonates admitted to NICU neonatal, death occurred in 63.8%. Among survivors at discharge, the rate of severe brain injury was 44.0%, the rate of retinopathy of prematurity was 58.3% and the rate of any serious neonatal morbidity was 100% [24].

Roberts et al. concluded that serial transabdominal amnioinfusions showed no significant difference in the outcome of maternal and perinatal outcome. The perinatal mortality was 19/28 vs. 19/28. The positive fetal survival effect of serial AI was unfortunately counterbalanced by an increased risk of neonatal death: 14 neonates died in the AI group vs. 9 in the control group. It is possible that the use of saline solution for AI was inappropriate due to the large deviations from normal human amniotic fluid [17,18].

Thus, the accumulation of sodium and chloride would disturb the sodium–potassium pump located in the plasma membrane of human cells and could be influencing organs’ performance, e.g., cardiac, lung and brain. These adverse effects of the instillation fluid could explain the high mortality rate after AI in this study.

Moreover, repetitive puncture from AI method would increase the risk of separation of amniotic membrane from the uterus, abruption of the placenta and injury to the umbilical cord, thus causing a trauma to the fetus.

Van Kempen et al. performed a randomized controlled trial in women with PPROM at 16 0/7 to 24 0/7 weeks of gestation with oligohydramnios. Participants were allocated to transabdominal amnioinfusion weekly or no intervention until 28/0 weeks of gestation. The primary outcome was perinatal mortality. Perinatal mortality rates were 18 of 28 (64%) in the amnioinfusion group vs. 21 of 28 (75%) in the no-intervention group (relative risk 0.86, 95% CI 0.60–1.22, *p* = 0.39) [48].

**Search reviews:** The general benefit of serial AI results from the restoring of the amniotic fluid protecting the fetus from compression of the umbilical cord and mechanical compression of the thorax, allowing normal fluid flow into the lungs and thereby preventing fetal lung hypoplasia [19,46,49,50]. Additionally, it protects the fetus from postural deformities. The spreading of infection is inhibited by dilution or by the infused solution itself. Obviously, the latter effect should be enhanced by the application of continuous AI due to enhanced dilution by continuous flush-out of bacteria and inflammatory compounds. The procedural problems of performing continuous AI could be solved by the recent development of a subcutaneously implanted catheter system [12,13,20,51].

Our search of the literature revealed five reviews of relevance [4,45,49,50,52,53].

The review of Hofmeyr (2014) assessed the effects of AI with standard solutions versus no AI for third-trimester PPROM and considered five randomized controlled trials, three of them with transcervical AI and two with transabdominal AI, including data from 241 women in total [45]. For transabdominal AI, the evidence grade was moderate for neonatal death, neonatal sepsis/infection and maternal puerperal sepsis and low for pulmonary hypoplasia [45]. The authors concluded that the results are encouraging but more studies are needed.

The review of Kozinszky (2014) analyzed eight published studies (case series) about amnioinfusion for treatment in severe mid-trimester oligohydramnios after PPROM [53]. They concluded that amnioinfusion, compared to expectant management, significantly improves the perinatal outcome, reduces the risk of postural deformity and prolongs the pregnancy in severe second-trimester oligohydramnios in both idiopathic cases and those involving PPROM.

Preterm premature rupture of membranes (PPROM), together with oligohydramnios before 26 weeks, can delay lung development and can cause pulmonary hypoplasia; the critical interval is between week 16 and 26. Restoring the amniotic fluid volume by transabdominal amnioinfusion might prevent abnormal lung development and might have a protective effect for neurological complications, fetal deformities and neonatal sepsis. Therefore, van Teffelen (2013) aimed to assess oligohydramnios secondary to PPROM before 26 weeks but could not identify randomized controlled trials comparing transabdominal AI with no AI [49,50]. They concluded that further research focusing on PPROM occurring very early (<26 week) is needed [49].

In 2012, Porat et al. reviewed serial transabdominal amnioinfusion from RCTs and observational studies [52]. Two identified RCTs were on women with PPROM between 24 and 34 weeks; one quasi-randomized study included women with PPROM before 26 weeks [52]. The meta-analysis of the observational studies resulted in significant prolongation of latency, reduction of perinatal mortality, decreased rate of pulmonary hypoplasia and reduced risk of neonatal death. The same tendency was seen in the RCTs, but it was statistically non-significant. From two RCTs, a decreased rate of infectious complications was observed in the AI group. Porat et al. concluded that transabdominal amnioinfusion for early PPROM may improve early PPROM-associated morbidity and mortality rates, but more RCTs are needed to improve the evidence [52].

Three publications evaluated performance- and safety-relevant information of continuous amnioinfusion by using amniotic fluid solution (AFS). Furthermore, the first clinical experience with AFS was gained at the Martin-Luther-Universität Halle-Wittenberg by PI (MT) [13]. Eighteen case reports are provided describing the successful administration of AFS by continuous amnioinfusion. In total, the important clinical benefit of AFS is the prolongation of pregnancy, thereby improving the outcome and prognosis of the preterm infant. The complications are generally expected to be the same as those that can be caused by PPROM itself and by the procedure of amnioinfusion with standard solutions, but to a less extent. Complications due to the fluid composition are not reported, and, if any, they are expected to be mild or infrequent due to the physiologic composition of AFS. The positive effect of continuous amnioinfusion through the subcutaneously implanted perinatal port system with Amnion Flush Solution in “classic PPROM” less than 26 (28)/0 weeks’ gestation shows promise but has not been evaluated in a prospective randomized trial. Our feasibility study suggested that continuous amnioinfusion prolongs the mean duration of the PPROM delivery interval for 49 days (range, 9–69 days), improving neonatal outcome [4,12,13,20,21,51].

The patients treated with Jonosteril^®^ (Fresenius Kabi GmbH, Germany), Sterofundin^®^ and isotonic NaCl (B. Braun AG, Melsungen, Germany) or lactated Ringer’s solution (Baxter, Germany) reported significantly increased diuresis, probably triggered trans-planetary by a fetal response to increased NaCl, fluctuation of osmolality and missing microelements, also referred to as the “Salzgurken effect” [4]. The electrolyte solutions for the continuous amnioinfusion were replaced in 2012 by artificial amniotic fluid (now Amnion Flush Solution, CE0483, Serumwerk AG, Bernburg, Germany) without any adverse events [4,12,13].

However, two groups from Japan in recently published retrospective studies (2020) were not able improve the neonatal outcome by using the low-rate amnioinfusion with Ringer’s lactate solution (40 mL/h) [14,15]. The authors mentioned the high frequency of catheter dislocation (60%) and lack of pump infusion in many cases [14,15]. The missed positive effect of the prolongation of the PPROM-delivery interval by two weeks onto healthy neonatal survival in these studies could be explained by “Salzgurken effect” of *off-label used* saline solution for a long time with a very high deviation of many parameters compared to human amniotic fluid (Table 3) [4].

Fetal skin in second trimester is still very thin and permeable. It is a matter of common knowledge that the fetus swallows and inspirates/expirates amniotic fluid. Gilbert and Brace indicated that the fetus swallows 200–250 mL/kg/day amniotic fluid [54]. Continuous amnioinfusion with normal saline solution significantly increased plasma Na^+^ and Cl^-^ concentrations in fetal sheep [55]. The amniotic fluid is a very complex hypoosmotic solution with an alkaline pH; low concentration of the elements Cl^−^, K^+^ and Na^+^; and the presence of trace elements, surfactants and many other substances [56].

Trace elements such as copper, zinc and selenium are needed for many enzymes and cofactors. They function as free radical scavengers and help to protect from oxidative stress. Several antioxidant enzymes are metal-dependent, such as Cu-Zn superoxide dismutase (SOD) and selenium-dependent glutathione peroxidase (GSH-Px) [57]. It could be shown that a deficiency in these trace elements may result in preterm birth and in clinical signs of the fetus such as poor growth, immature gastrointestinal tract and disturbed development of organs [58]. The zinc content of the amniotic fluid has an important metabolic role, and a positive correlation between zinc concentration of the amniotic fluid and fetal weight and length was found. The zinc content of the amniotic fluid increases significantly during the third trimester [59].

Selenium deficiency in females is associated with infertility and spontaneous abortion, suggesting a role for selenium-requiring proteins during embryonic development [60]. The amniotic selenium level significantly decreases with the progress of normal pregnancy. This might be in part attributed to the greater demand for the nutrient by the fetus during late pregnancy [61].

Therefore, the AFS should contain the trace elements copper, zinc and selenium in concentrations, as reported for natural human amniotic fluid. Obviously, the concentrations of copper and selenium in AFS match well with the reported concentrations from the literature. The reported zinc concentrations in amniotic fluid from different studies showed a large variation (0.3 to 7.6 µmol/L*). The concentration of 2.6 µmol/L in AFS reflects this variation and is justified due to the fact that zinc is essential and highly required by the fetus [62].

The change of physiological fetal surroundings for a long period by using amnioinfusion with simple electrolyte solutions could destroy, in all probabilities, the fetal programming. Hypernatremia-induced osmotic demyelization disorders and central pontine and extrapontine myelinolysis are well-known [63]. Chhabra et al. described the extra-pontine myelinolysis induced by hypernatremia [64]. The combination of the very immature brain–blood barrier of the fetus with the permeable skin and swallowing of a relatively large amount of electrolyte solution deteriorates the fluctuations of the NaCl concentration of the fetal brain. This could explain the high neonatal mortality rate after serial amnioinfusion in the Roberts et al. study and very moderate success of continuous amnioinfusion from using Ringer’s lactate solution (inappropriate to human amniotic fluid) described in the retrospective Japanese studies [14,15,17,18].

In summary, the standard treatment options of the classic mid-trimester PPROM with oligo/anhydramnion, including RDS prophylaxis and broad-spectrum antibiotics, hardly improve the neonatal outcome. The extension of the standard therapy by continuous amnioinfusion—the Amnion Flush Method—could improve the neonatal survival without major morbidities. In 2020, the German Federal Ministry of Education and Research funded this prospective multicenter randomized study investigating the effect of continuous amnioinfusion in patients with classic PPROM with oligo/anhydramnion between 22/0 (20/0) and 26/0 WG with Amnion Flush Solution (100 mL/h, 2400 mL/d) through a transcutaneous perinatal catheter with an anchor system compared with the standard PPROM therapy (ClinicalTrials.gov: NTC04696003).

